### First phase: the individual interview

The clinical context of this decision study is the use of antithrombotic agents to treat chronic non-valvular atrial fibrillation. Both patients and clinicians will go through an individual highly scripted interview. To determine their strength of preference for use of antithrombotic agents we will conduct a probability trade-off exercise. This will answer the first research question and will allow us to determine if there is a difference and if present the magnitude of the difference in strength of preference for treatment between patients and clinicians, the second research question.

To partially answer the third research question (whether differences in utilities for the relevant health states explain differences in treatment preferences) we will ask participants to assign relative value to the relevant health states using a visual analog scale (also known as the feeling thermometer). The complete elicitation of treatment preferences and utilities will take approximately 15 minutes. The patients will receive the mini-mental state examination and 2 additional "screening" scenarios to gauge their ability to participate in the probability trade-off exercise. Thus, we expect patient interviews to take 45 minutes and clinician interviews to take 30 minutes to complete.

To account for order effects, we will randomize the order in which participants complete the exercises (probability trade-off and feeling thermometer) and the health states within the feeling thermometer (mild stroke, major stroke, taking warfarin, taking aspirin, severe bleeding). Clinicians could answer questions thinking about what they would choose for themselves (if they were to have atrial fibrillation) or what they would recommend to their patients. To eliminate this ambiguity (and study this potential effect), and following the method by Cohen and Pauker [22], we will randomize clinicians to instructions that ask them to participate and complete the preference elicitation tasks in the role of a patient or as a clinician making a recommendation to a patient.

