#### Probability trade-off

We propose to use the probability trade-off technique to determine the strength of preference patients and clinicians have for antithrombotic use to prevent strokes associated with atrial fibrillation. We have described the conduct of the probability trade-off exercise for the same decision context [12]. During the interview, the researcher, following a pre-written script, presents information both verbally and visually with the use of colored pictorial flip charts, known as decision boards (Figure 2). Participants will review the decision boards describing major and minor stroke, major bleeding, and inconveniences and costs of treatments. After presenting the descriptions, interviewers will ask participants if the scenarios reflect their own appreciation of the issues involved in the decision and will note any discrepancies. Whatever their response, we will ask participants to provide responses assuming that the scenarios represent an accurate and complete characterization of the health states. This instruction seeks to reduce information asymmetry between patients and clinicians and between specialists and generalists. Also, we will use the same decision boards and the same scripts to interview both patients and clinicians. The only difference in the scripts is that clinicians, when randomized to respond like a clinician making a recommendation to a patient, would need to indicate whether they would recommend using warfarin at the given risks while patients would need to indicate whether they would *use *warfarin at the given risks.

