#### The feeling thermometer

To further understand the treatment preferences elicited using the probability trade-off and capture the values patients and clinicians place on the health states that may result from their choice, namely strokes and bleeds, we will conduct preference-elicitation exercises using the feeling thermometer, a visual analogue scale [27,28]. When completing the feeling thermometer patients choose the score on the thermometer that represents the value they place on the health state they are being asked to evaluate. The feeling thermometer is anchored at death (0) and perfect health (100). The feeling thermometer will allow us to check understanding of the relative severity of the health states in question (i.e., patients should assign a lower value (a value closer to 0) to a major stroke with severe and permanent disability than a minor stroke).

Because the visual analogue scales may be prone to context bias, that is rating of one state may influence rating of other states [29,30], we will randomize the order in which participants will consider the health states to minimize this bias. We will ask participants to consider the following health states one at a time on the feeling thermometer:

▪ Major and minor strokes. We will inform patients that the sequelae of the stroke will last for the patient's life expectancy.

▪ Severe bleed. We will inform patients that they will have a major bleed within the first year of taking the antithrombotic agent but will not have another severe bleeding event for the rest of their life

▪ Taking warfarin

▪ Taking aspirin

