Our review of the evidence suggests that it is more likely that we will confirm substantially different treatment choices in clinicians and patients. This result would suggest that current low rates of anticoagulation in atrial fibrillation reflect clinician and not patient values, and mandate urgent development and testing of interventions to increase rates of anticoagulation, and thus prevent unnecessary strokes. Such findings would not, however, explain why clinician and patient choices differ. We see two leading possibilities. One is that, relative to patients, clinicians experience the post-stroke state as relatively less aversive, and having a gastrointestinal bleed as relatively more aversive, than do patients. The second explanation is that clinicians and patients share the same values for stroke and bleeding, but the circumstances of clinical decision-making lead clinicians to make different choices. In particular, we hypothesize that omission bias associated with efforts to reduce clinician-generated risk, may explain the results. This explanation posits that clinicians put more weight on commission of a behavior that leads to adverse consequences (bleeding through warfarin administration) than an omission of behavior that could lead to beneficial consequences (stroke prevention through warfarin administration). We will explore this issue through direct measurement of utilities for stroke and bleeding, and through focus groups with the participating clinicians.

On completion of this study, we will hope to achieve major advances in understanding clinician and patient decision-making in atrial fibrillation. Our anticipated results will challenge investigators, medical educators, and health care providers to develop and test strategies to deal with differences in clinician and patient choices. Our results will guide the development of these strategies, which may include innovations in undergraduate and post-graduate education, enhancements to the clinical encounter to facilitate patient-clinician communication and shared decision-making, increasing use of decision support tools in clinical practice, and monitoring and feedback of clinician success in providing optimal anticoagulation in patients with atrial fibrillation. For example, our experience using decision boards in this study will inform the organization and conduct of a randomized controlled trial to test their efficacy in helping patients with atrial fibrillation make informed choices.

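### Read literally, the randomised clinician role covers the feeling thermometer as well as the trade-off; the two sections that describe it must be reconciled, or a role effect could pass for, or hide, a difference in values

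*Protocol article*

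**What the plan says.** In the protocol article, the section First phase: the individual interview names two exercises, the probability trade-off and the feeling thermometer. It then says that clinicians will be randomised to "complete the preference elicitation tasks in the role of a patient or as a clinician making a recommendation to a patient". The plural carries no exception, and the section The feeling thermometer puts that instrument in the same class: "we will conduct preference-elicitation exercises using the feeling thermometer".

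The section Probability trade-off describes the role in terms of a treatment choice. "clinicians, when randomized to respond like a clinician making a recommendation to a patient, would need to indicate whether they would recommend using warfarin", whereas patients say whether they would use it. This is introduced as the only difference in the scripts. No section says what a recommender should do when rating a health state.

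The thermometer is described in terms of the respondent's own value: "patients choose the score on the thermometer that represents the value they place on the health state they are being asked to evaluate". Its purpose is to help answer "whether differences in utilities for the relevant health states explain differences in treatment preferences".

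Under Research question 3 (Differences in utilities between patients and clinicians), the five utilities are compared between patients and clinicians by Mann-Whitney and t tests, then correlated with *b* and used as predictors of *b*. Role is not mentioned there. It is a grouping factor for *b* under Research question 1.

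**The concern.** The Discussion offers two explanations for a difference in treatment choice. One is that "clinicians experience the post-stroke state as relatively less aversive, and having a gastrointestinal bleed as relatively more aversive, than do patients". The other is that clinicians share patients' values but the setting of clinical decision-making changes what they choose. Measured utilities, together with the focus groups, are meant to distinguish these.

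That works best if the utilities are free of the decision role. The stated reason for the role randomisation is the ambiguity between choosing for oneself and recommending to a patient, and both of those are choices. Rating a health state involves no choice, so under a recommender instruction it is undefined whose value is being scored. If the instruction moves the scores, the pooled comparison mixes two quantities. An effect belonging to the second explanation could then appear as evidence for the first, or could cancel a real difference in values. If role moves both *b* and the utilities, it also adds an association between them among clinicians, which the regression of *b* on utilities could present as values explaining preference.

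**Working it through.** **Which tasks carry the role**

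- First phase section: the role covers the preference elicitation tasks, with both exercises just named.
- The feeling thermometer section: the thermometer is a preference-elicitation exercise. Together these put the role on the thermometer.
- Probability trade-off section: the only script difference is recommend versus use. If this covers the whole interview, it contradicts the First phase section. If it covers only the trade-off scripts, the recommender's thermometer instruction is not given anywhere.

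**Inputs**

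- 96 patients, 96 clinicians, α = 0.05 (Sample size estimation and Table 2); two-sided testing assumed.
- Recommender share *f*: not stated. 0.5 assumed (48/48), with 1/3 and 2/3 as the range.
- Role shift *r*, in SD units of a thermometer score: not in the document. 0.2 to 0.8 assumed.
- Clinicians' own values set equal to patients'.

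**The plan's own figure.** Power ≈ Φ(d/√(1/n₁ + 1/n₂) − 1.96). For d = 0.4 and 96 per group: √(2/96) = 0.1443; 0.4/0.1443 = 2.77; Φ(0.81) = 0.79. Table 2 states .79. All 16 cells of Table 2 reproduce to within two percentage points, so no stated figure is in dispute.

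**False value difference.** With equal own values, the expected pooled difference is *f*·*r*. The rejection rates come from 10,000 simulated studies per setting, using unit-SD normal scores, the shift applied to recommenders only, and a t test of patients against all clinicians.

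| Role shift *r* (SD) | Pooled difference at *f* = 0.5 | Rejects, all clinicians | Rejects, patient-role clinicians only |
|---|---|---|---|
| 0.2 | 0.5 × 0.2 = 0.1 | 10% | 5% |
| 0.4 | 0.5 × 0.4 = 0.2 | 27% | 5% |
| 0.6 | 0.5 × 0.6 = 0.3 | 53% | 5% |
| 0.8 | 0.5 × 0.8 = 0.4 | 77% | 5% |

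At *r* = 0.4 the rate is 15% if one third are recommenders and 44% if two thirds are.

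**Masking.** A true difference of 0.4 SD with an opposite role shift of 0.4 SD in half the clinicians leaves 0.4 − 0.5 × 0.4 = 0.2 SD. Simulated power is then 28%, against the 0.79 planned.

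**Patient-role clinicians only (48 against 96 patients).** √(1/48 + 1/96) = 0.1768; 0.4/0.1768 = 2.26; Φ(0.30) = 0.62. The difference detectable at 80% power is (1.96 + 0.84) × 0.1768 = 0.50 SD, compared with (1.96 + 0.84) × 0.1443 = 0.40 SD with all 96.

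**The case against.** The strongest reply is that the role was never meant for the thermometer. The trade-off section limits the script difference to one question, and the rationale for the role speaks of choosing and recommending. On that reading every clinician rates for themselves and nothing is contaminated. This stands as a possible intent, but the First phase section then says something else and needs correcting.

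Secondly, role is randomised and its effect is deliberately studied. The focus group agenda includes a question on how clinicians' answers differed by role, not limited to *b*. The role effect on utilities can therefore be estimated without changing the design. That is right. The lack of a role term for utilities, taken alone, could also be detail that an article leaves to the full protocol. What remains is a conflict between two stated sections, which bears on a comparison the article does state.

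Thirdly, no figure in the document supports any role effect on ratings. For scale, the whole patient–clinician difference in *b* in the prior study was 0.9 with SDs of 0.9 and 0.8, so 0.9/√((0.81 + 0.64)/2) = 0.9/0.851 ≈ 1.06 SD. A role shift of 0.8 SD on the thermometer would be about three quarters of that (0.8/1.06 = 0.75). The upper rows of the table therefore assume large effects.

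Finally, the thermometer answers Research question 3 only in part, by the article's own account. No single t test decides between the two explanations.

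**Conclusion.** The two sections disagree, or at best leave open, whether the recommender role applies to the thermometer, and they must be reconciled. If it does apply, the pooled comparison of utilities and the regression of *b* on utilities mix own values with recommender-role ratings. A false value difference would then arise in about 10% to 77% of studies for role shifts of 0.2 to 0.8 SD, assuming a 1:1 split, equal own values and normal scores. A role effect in the other direction could hide a real difference.

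A reader might infer more: that half the clinicians' scores certainly do not measure their own values, or that a spurious finding is likely. The document supports neither. It does not settle whether the role reaches the thermometer, does not state the allocation ratio, and gives no estimate of a role effect on ratings. Table 2 is correct. This is a point to settle before interviews start, not a fatal flaw.

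**What to change.** **Preferred.** State in the First phase section that the randomised role applies to the probability trade-off only. Have every clinician, in both arms, complete the thermometer for the value they themselves place on each state, using the patients' script. Because the order of the exercises is randomised, give the own-value instruction immediately before the thermometer to limit carry-over. This needs a sentence in the protocol and in the script and no extra interviews, and it keeps all 96 clinicians and the 0.79 power at 0.4 SD. There are two small costs: the role effect on utilities is no longer studied, and clinicians in the recommender arm switch perspective between tasks, so their *b* and their utilities come from different roles.

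**If the role is kept on the thermometer.** Say what a recommender is asked to rate, and amend the Research question 3 analysis to:

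- report the randomised role contrast in utilities;
- include role in the regression of *b* on utilities;
- base the comparison that speaks to different values on patient-role clinicians against patients;
- restate power for that comparison as about 0.62 at 0.4 SD, with about 0.50 SD detectable at 80% power, assuming 48 per role.

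The cost is power: the claim in Sample size estimation of at least 80% for a 0.4 SD difference in mean utilities would no longer hold for that comparison.

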#### The health states

The decision to use antithrombotic agents in patients with atrial fibrillation at risk of stroke involves a choice between aspirin or warfarin use. "No therapy" is a realistic option only for the lowest risk patients, or those with a serious bleeding problem. Decision analyses [23] and decision support [24] investigators have shown that the choice of antithrombotic therapy is sensitive to preferences for the following health states: major and minor stroke, major gastrointestinal bleed, and taking either warfarin or aspirin daily (including the need for periodic monitoring and lifestyle modification with warfarin). We plan to use the same health state descriptions for stroke and major bleed that we used in a previous study [12], which in turn were modified from Man-Son-Hing et al [25]. These are almost identical to other descriptions in the literature and have three advantages: (1) have been published before and were deemed valid to peer investigators in the field of decision making; (2) have been used with clinicians for the conduct of a decision study and therefore were deemed valid and understandable to participants similar to those we propose to enroll for the present study; (3) their use will allow our results to compare to other studies in this field, including our previous study in a different sample of clinicians.

#### Probability trade-off

We propose to use the probability trade-off technique to determine the strength of preference patients and clinicians have for antithrombotic use to prevent strokes associated with atrial fibrillation. We have described the conduct of the probability trade-off exercise for the same decision context [12]. During the interview, the researcher, following a pre-written script, presents information both verbally and visually with the use of colored pictorial flip charts, known as decision boards (Figure 2). Participants will review the decision boards describing major and minor stroke, major bleeding, and inconveniences and costs of treatments. After presenting the descriptions, interviewers will ask participants if the scenarios reflect their own appreciation of the issues involved in the decision and will note any discrepancies. Whatever their response, we will ask participants to provide responses assuming that the scenarios represent an accurate and complete characterization of the health states. This instruction seeks to reduce information asymmetry between patients and clinicians and between specialists and generalists. Also, we will use the same decision boards and the same scripts to interview both patients and clinicians. The only difference in the scripts is that clinicians, when randomized to respond like a clinician making a recommendation to a patient, would need to indicate whether they would recommend using warfarin at the given risks while patients would need to indicate whether they would *use *warfarin at the given risks.

**Figure 2 F2:**
[figure not shown]
**Section of the decision board for probability trade-off**[1]**comparing outcomes of****2 years of warfarin use****vs. aspirin among 100 patients with atrial fibrillation, as used in our preliminary study**[12].

During the individual interview, we will present complete information about the risks, benefits, and inconveniences of warfarin and aspirin. To demonstrate how we will determine a patient's threshold for accepting a treatment we will discuss the scenario for determining the maximum bleeding increase acceptable for warfarin therapy (i.e. the bleeding threshold for warfarin) in a comparision of warfarin vs. aspirin.

The scenario is based on the absolute effects of both drugs on 100 patients over a two-year period. We will use a probability trade-off with the elicitation method of "ping-ponging" to determine participant's thresholds. The interviewer will systematically vary the risk of bleeding with warfarin (alternating between high and low risk of bleeding) to determine the maximum acceptable increase in the risk of bleeding with warfarin, given a fixed reduction in the risk of stroke with warfarin relative to a fixed risk of bleeding and stroke with aspirin. The alternating presentation of high and low risk of bleeding may reduce "start point bias" resulting from starting the exercise at the point of known efficacy and safety of the medications.

Given the risk of bleeding with aspirin is two patients in a hundred (over a two year period) we will offer probabilities from 0 additional bleeds with warfarin to 38 additional bleeds with the use of two sets of flipcharts (one exploring up to 17 and one exploring up to 38 additional bleedings). In our previous study, we compared warfarin versus no treatment and the mode for patients' bleeding threshold was 22 additional bleeds per 8 fewer strokes with warfarin therapy (10.3 [6.1] and 17.4 [7.1] additional bleeds for physicians and patients respectively) [12]. The 22 additional bleeds corresponded to the maximum bleeding threshold explored. Since in this proposal the number of strokes avoided is 3 (in the comparison of warfarin versus aspirin), we will increase the range explored by going up to 38 additional bleeds. Additionally, in the case of participants willing to take warfarin given an increased risk of an additional 38 bleeds, we will ask them, without the use of flipcharts, what is the maximum number of bleeds they would accept before switching to aspirin (being 100 the maximum). This range should ensure capturing the preferences of all clinicians and most patients interviewed.

Initially, participants will complete two eligibility scenarios that compare the outcomes of stroke and bleeding with two ficticious drugs with the same adverse effects, burdens and cost, but with major differences in terms of stroke reduction. If participants do not select the medication with the higher stroke reduction in both instances they will be excluded as their choice reflects inadequate comprehension.

The decision boards will reflect the best available evidence, namely from the meta-analysis of warfarin vs. aspirin for atrial fibrillation [11] (Table 1). Our scenario will start with a statement of the baseline risk–"with aspirin treatment there is a baseline risk of a major or minor stroke over the next two years of 8 patients out of 100 and a risk of severe bleeding over the next two years of two patients out of 100. In the case of warfarin there is a baseline risk of major or minor stroke over the next two years of 5 patients out of 100". We will then present that risk of bleeding using a flipchart. In this first flipchart we will start randomly with either no additional bleedings or with up to 17 additional bleeds. If the participant decides that she would still take warfarin with 17 additional bleeds, with the help of a second flipchart, we will offer up to 38 additional bleeds (starting either at 18 additional bleeds or at 38 and using the same "ping-ponging" method). In the case of a patient or physician accepting the 38 additional bleeds we will ask her what is the maximum number of bleeds she would accept before switching to aspirin.

**Table 1 T1:** Summary of results of meta-analysis of warfarin vs. aspirin in patients with atrial fibrillation [11]

